### **8.2.3 Laboratory inspections and other safety assessment abnormalities reported as adverse events and serious adverse events**

Any abnormal laboratory test results (hematology, clinical biochemistry, urinalysis) or other safety assessments (for example, ECG, imaging scans, vital signs measurement), including worsening than baseline and events of clinical significance with the researcher’s medical and scientific judgments will be reported as AE or SAE.

In addition, if any laboratory test results or other safety assessments lead to interventions (including permanent discontinuation of trial treatment, dose reduction,

and/or administration suspension/delay), the relevant AE or SAE should be recorded.

Any new primary cancer must be reported as SAE.

However, for any clinically significant safety assessment related to the underlying disease, unless the result is judged by the investigator more serious than expected, should not be reported as an AE or SAE.

#### 8.2.4 Assessment of the severity of adverse events

Researchers need to follow the definition of severity in accordance with NCI-CTCAE (version 5.0) to describe the highest severity of AE. If the AE is judged as SAE, the CTCAE classification recorded on the AE page of the eCRF must be consistent with the description of the NCI-CTCAE (version 5.0) classification.

##### Standard of Adverse Event Severity

| Grades | Equivalent                     | Description                                                                                                                                                                      |
|--------|--------------------------------|----------------------------------------------------------------------------------------------------------------------------------------------------------------------------------|
| 1      | Mild                           | Observation only and normal daily activities not affected.                                                                                                                       |
| 2      | Moderate                       | Daily activities affected; no treatment or medical intervention indicated although they can relieve symptoms or improve life quality.                                            |
| 3      | Severe                         | Inability to work or complete daily activities; treatment or medical intervention indicated to improve the quality of life or relieve symptoms; not immediately life-threatening |
| 4      | Life threatening or disability | Direct life threatening or permanent mental or physical damage; inability to work or carry out daily activities; urgent medical intervention indicated.                          |
| 5      | Death                          | Adverse events result in death.                                                                                                                                                  |

Pay attention to the difference between intensity and severity of AE. Serious AE is not necessarily SAE. For example, a headache can be severe (significantly affecting the patient's daily function) while not necessarily SAE, unless in agreement with one of the above SAE criteria.

#### 8.2.5 The causal relationship between adverse events and study drugs

The causal relationship between adverse events and the study drug is as follows:

- Definitely irrelevant: No study drug is used, or there is no correlation between the use of study drug and the time of the AE, or there is a clear cause of the AE.

- Possibly irrelevant: There is evidence of the use of the study drug and the AE that occurred may be better explained by other reasons. The withdrawal reaction is negative or unclear.

- Possibly related: There is evidence of the use of the study drug and the temporal correlation between the occurrence of AE and the use of study drug is reasonable. AE can be explained by other reasons. The drug withdrawal reaction was positive.

- Definitely related: There is evidence of the use of study drugs. The occurrence of AEs and the use of study drugs are in a reasonable time sequence. AEs explained by study drugs are more reasonable than other reasons. The drug withdrawal reaction was positive and the reaction is positive for repeated medication (if feasible).

- Unable to judge

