| Bone marrow aspiration and biopsy  | × |   |   |   |   |   | × |   |   |  |
| Biomarker collection                            |   |   |   |   |   |   |   |   |   |  |
| Peripheral blood                   | × | × | × | × | × | × | × |   |   |  |

Note.

- End of treatment (EOT): the date of termination of study treatment is defined as the date on which the investigators confirms that the subject needs to terminate the study treatment for any reason. The time window of termination of study treatment visit is +28 days.
- Safety follow-up: the time window of safety follow-up was 30 days after the last study  $\pm$  3 days; If the study treatment termination visit occurs within the time window of safety follow-up, the same examination items need not be repeated.
- Radiography follow-up: except for the subjects who stopped taking drugs due to the judgment of disease progression according to imaging evaluation, the imaging evaluation was continued according to the established time until the occurrence of imaging disease progression, the start of new anti-tumor treatment, withdrawal of informed consent, death or the end of the study (whichever occurs first)
- Survival follow-up: after the last study, the survival of the subjects was followed up by telephone every 12 weeks, and the survival of the patients with disease progression was followed up every 8 weeks.
- Combined use of drugs: The combined medication within 30 days before the screening visit was recorded until the safety follow-up was completed.
- Adverse events: all AE were recorded from the signing of informed consent until 30 days after the last study treatment; SAE should be recorded until 90 days after the last study treatment or the start of new anti-tumor treatment, whichever occurs first. After that, only SAE related to the study treatment should be recorded.
- ECG: ECG will be in screening period, treatment period (3 weeks)  $\pm$  3 days) and safety follow-up, ECG examination can be added if necessary.
- Height, weight and vital signs: height examination was only carried out in the screening period, weight examination was only carried out in the screening period, study treatment termination visit and safety follow-up; Vital signs include body temperature, pulse rate, respiratory rate and blood pressure.

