**Note**

a: Resume the administration after the symptoms improvement to grade 0-1 or baseline level.

b: For hypophysitis, adrenal insufficiency, thyroid insufficiency/hypothyroidism, and type 1 diabetes, resume the administration if they are fully controlled and only need physiological hormone replacement therapy.

c: For abnormal grade 4 laboratory test results, the decision whether to terminate the medication should be determined based on the accompanied clinical symptoms or signs and the clinical judgment of the investigator.

The maximum interval allowed for drug suspension is 12-weeks. If it is not possible to recover to the state where sintilimab can be reused within 12 weeks, the subject will be permanently suspended for sintilimab administration and then enter the follow-up phase. Except for the following two cases:

- Due to the application of glucocorticoids for the treatment of irAE, sintilimab was suspended for more than 12 weeks during the process of glucocorticoid reduction. Under this condition, it is necessary to discuss with the sponsor to decide whether to continue sintilimab treatment. The radiological examination for efficacy evaluation is still carried out as planned and is not affected by the suspension of medication.
- Due to treatment of AEs unrelated to sintilimab, it was suspended for more than 12 weeks. Under this condition, it is necessary to discuss with the sponsor to decide whether to continue sintilimab treatment. The radiological examination for efficacy evaluation is still carried out as planned and is not affected by the suspension of medication.

At the beginning of each treatment course, all hematological and non-hematological toxicities must be restored to no more than Grade 1 or the baseline level and the investigator considers it appropriate to proceed to the next course. If this condition is ineligible, the administration can be extended for 14 days. Once it's over 14 days, the investigator will decide whether the patient needs to withdraw from the study based on the risk-benefit ratio.

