### **5.7 Toxicities of chidamide**

The safety data of chidamide in PTCL patients were mainly derived from a pivotal, single-arm, open-label, phase II clinical trial (n = 83) and an exploratory, single-arm, open-label, phase II clinical trial (n = 19). In pivotal Phase 2 clinical trials in PTCL, patients were treated with 30 mg twice weekly for an average of 4.4 months. In the exploratory phase II clinical trial of PTCL, patients in the two groups received 30 mg and 50mg, respectively, and patients in both groups took the drug twice a week for two weeks followed by a one-week rest period after discontinuation. The mean duration of treatment for all patients in this trial was 7.6 months. Common adverse reactions observed in clinical trials are hematological adverse reactions, including platelet count decreased, white blood cell or neutrophil count decreased, hemoglobin decreased; systemic adverse reactions, including fatigue, fever; gastrointestinal adverse reactions, including diarrhea, nausea and vomiting; metabolic and nutritional system adverse reactions, including decreased appetite, hypokalemia and hypocalcemia; and other adverse reactions, including dizziness and rash. Serious adverse events of the 83 patients in the pivotal Phase II clinical trial of chidamide, 7 patients (8.4%) experienced

8 serious adverse events (SAEs), including 1 patient each with increased white blood cell count, sudden cardiac death, decreased platelet count, lactic acidosis, intestinal perforation, and gangrene of the right toe, of which 3 (sudden cardiac death, lactic acidosis, and intestinal perforation) led to death.

For more information, please refer to the drug manual. In exceptional cases, oral antiemetics may be administered to prevent gastrointestinal reactions.

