### **5.13 Criteria for discontinuation of study drugs**

If any of the following adverse events related to the study drug occur, the administration of research drug should be permanently discontinued:

1. Grade 3-4 pneumonia;
2. Grade 3-4 hepatitis (elevation of ALT, AST or total bilirubin);
3. Grade 3-4 decrease of cardiac function;
4. Grade 3-4 pancreatitis;
5. Grade 3-4 allergic reactions;

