## **8 Safety assessment**

### **8.1 Safety Endpoint**

Safety monitoring begins when the ICF is signed and continues until 4 weeks after the end of treatment or until the beginning of another anti-tumor treatment (whichever occurs first). The safety endpoints of this study are as follows:

- The incidence, type and severity of adverse events during treatment are classified according to NCI-CTCAE (version 5.0). Research-related TEAE, SAE, Grade 3 or higher non-hematological AE, Grade 4 hematological AE and permanent discontinuation due to TEAE.
- The frequency and causes of deaths that occurred within 4 weeks ( $\pm 3$  days) of the last medication.
- Safety laboratory inspections classified according to NCI-CTCAE (version 5.0).
- Vital signs, ECG, full physical examination and ECOG physical status score.

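### The causality scale makes a positive drug-withdrawal reaction a condition of both related categories, so events without an assessable dechallenge cannot be classified as related

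*Protocol*

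**What the plan says.** Protocol 8.2.5 gives five causality categories.

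- **Definitely irrelevant:** no study drug was used, the timing does not fit, or there is a clear cause.
- **Possibly irrelevant:** the drug was used, other reasons may explain the event better, and "The withdrawal reaction is negative or unclear".
- **Possibly related:** the drug was used and the timing is reasonable. The definition ends with "AE can be explained by other reasons. The drug withdrawal reaction was positive".
- **Definitely related:** the timing is reasonable, the drug is the more reasonable explanation, and "The drug withdrawal reaction was positive and the reaction is positive for repeated medication (if feasible".
- **Unable to judge:** no criteria are given.

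Other sections use the result. Section 8.1 lists "Research-related TEAE, SAE, Grade 3 or higher non-hematological AE, Grade 4 hematological AE and permanent discontinuation due to TEAE". Section 5.13 says "If any of the following adverse events related to the study drug occur, the administration of research drug should be permanently discontinued". Item 1 of 5.12 and Table 1 in 5.5 are likewise limited to treatment-related or sintilimab-related events. Section 8.2.6 asks for a report to the ethics committee and regulators when many unexpected related events occur. The adverse-event note under the study flow chart, after setting the recording period for serious events, adds "After that, only SAE related to the study treatment should be recorded".

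**The concern.** A withdrawal reaction can be positive only if the drug is stopped, the patient survives long enough for the effect to be seen, and the event can reverse. The protocol foresees toxicities that fail one of these conditions, yet neither related category provides for them.

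What is at stake is the related-event summary for a two-drug combination that includes a dose-escalation part, where the safety profile is a secondary objective. A scale that cannot place such events in a related category understates attributed toxicity. It also leaves the rules that depend on attribution without a dependable trigger.

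**Working it through.** No arithmetic underlies the rule, so the check reads each category in 8.2.5 as a set of joint conditions and passes four kinds of event through it. Each event has plausible timing and no better alternative cause.

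| Event | Withdrawal reaction | Possibly or definitely related? | Possibly irrelevant? | Category left |
|---|---|---|---|---|
| Resolves on stopping | Positive | Can be met | No | A related category |
| Fatal before the effect of stopping is visible | Not observable | Not met | No: needs a better alternative explanation | Unable to judge |
| Irreversible after stopping | Negative | Not met | No: same reason | Unable to judge |
| Drug continued through the event | None exists | Not met | No: same reason | Unable to judge |

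The feasibility qualifier under definitely related most naturally covers only the rechallenge. Possibly related has no qualifier at all. Definitely irrelevant does not fit the last three rows either, because the timing is plausible and no clear other cause exists.

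**Does the protocol foresee such events?**

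1. *Treated through.* Table 2 in 5.6 gives rules for infusion reactions that it calls sintilimab-related, and describes grade 1 as needing no interruption. In 5.4, 40 of 85 patients with infusion reactions had grade 1: 40/85 = 47%. Table 1 lists suspension from grade 2 for pneumonia and diarrhea and from grade 3 for dermatitis, with none listed for lower grades.
2. *Persistent.* For hypophysitis, adrenal insufficiency and type 1 diabetes, the note under Table 1 says "resume the administration if they are fully controlled and only need physiological hormone replacement therapy". An event that still needs replacement has not shown a clear positive dechallenge.
3. *Fatal.* Section 5.7 describes serious events on chidamide, "of which 3 (sudden cardiac death, lactic acidosis, and intestinal perforation) led to death".

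**Circularity.** Sections 5.12 item 1, 5.13 and Table 1 ask whether the event is related in order to decide on suspension or stopping. Section 8.2.5 asks what happened on stopping in order to decide whether the event is related. For a drug still being given, neither can be settled first.

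**Which rules depend on the classification?**

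- *Dependent:* research-related events in 8.1, the report of unexpected related events in 8.2.6, 5.12 item 1, 5.13, Table 1, and the late-SAE note under the flow chart.
- *Not dependent:* SAE reporting within 24 hours and SAE follow-up (8.2.7), deaths within 4 weeks of last medication (8.1), and the grade-based chidamide reduction triggers (5.5).
- *Contradictory:* the flow-chart note limits late SAE recording to related events, while 8.2.7 keeps SAEs after follow-up reportable even when relatedness is ruled out.

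**The case against.** The strongest reply is that 8.2.5 does not say all conditions must hold together. Under a strict reading, 5.13 could not operate for any event where the drug had not already been interrupted, so that reading is probably not what was intended. This is fair as to intent. But the joint reading is the natural one for a list of criteria, and a scale that works only when sites set a written criterion aside will be applied differently across centres.

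A second reply is that a site may treat the end of an infusion as a withdrawal, since 5.6 says reactions usually clear within 24 hours of completion. Section 8.2.5 does not say so, and this would not help with fatal, irreversible or continued-dosing events.

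Third, events that cannot be judged are not thereby declared unrelated, and how they are counted in tables may be settled in an analysis plan not at hand. This stands in part: the missing counting rule alone would be no finding. The misfit in the related definitions is in the protocol's own text, and the expedited report and stopping criteria are protocol rules.

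Several stronger inferences are tempting but unsupported:

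- A reader might infer that these events drop out of every rule that uses causality. They do not: 8.2.6 ends follow-up on causality grounds only when the investigator confirms that the event is not related, and the late-SAE texts conflict.
- A reader might infer that deaths go unreported. Sections 8.1 and 8.2.7 capture them regardless of causality.
- A reader might infer a distorted MTD. The protocol states no causality condition for DLTs.
- A reader might project the chidamide deaths in 5.7 onto this trial. That section does not say they were drug-related, and they come from another population on monotherapy.

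**Conclusion.** The point holds in this form. As written, 8.2.5 has no related category for events whose dechallenge is impossible, negative or not attempted. With no better alternative explanation they fit only the unable-to-judge category.

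The direction of the error is clear: research-related events are under-counted, and the trigger for reporting unexpected related events becomes unreliable. Its size cannot be derived from the protocol. The 47% of infusion reactions at grade 1 shows only that events managed without interruption are common within one type of event; it does not estimate the bias in this trial.

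The events remain in the safety data. What is lost is their attribution. The conclusion assumes that the listed criteria are joint and that the feasibility qualifier covers only the rechallenge.

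**What to change.** - In 8.2.5, make a positive withdrawal reaction supportive rather than required in both related categories.
- Allow a not-assessable result where the event was fatal or irreversible, or the drug was not stopped.
- Remove an unclear withdrawal reaction as a marker of possibly irrelevant.
- State that unable-to-judge events count as related in the related-event tables and in safety reporting.
- Reconcile 8.2.5 with 5.12 item 1, 5.13 and Table 1, so that relatedness can be judged when those rules are needed. How the stopping criteria should then read is for the sponsor; none is proposed here.
- Reconcile the late-SAE note under the flow chart with 8.2.7.

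The cost is a few sentences in the protocol and matching text in the CRF instructions. The downside is a somewhat higher reported rate of related events.

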### **8.2.6 Handling and reporting of adverse events**

According to the Chinese GCP regulations, all AEs that occur during clinical research should take the following measures, regardless of which treatment group they belong to or whether related to the study drug:

1. The investigator should immediately take appropriate protective measures to ensure the safety of the patient and relevant experts should make a diagnosis and state the reason.
2. If the study is terminated, the investigator should also check the patient regularly and fill in the date of termination of the study (the date when the administration of the study drug was stopped), the reason for termination and the detailed process in the CRF.

3. The investigator should follow up all AEs that occur until any of the following condition occurs:
  - a) AE is alleviated or improved to the baseline level.
  - b) The researcher confirms that no further improvement is expected.
  - c) Death of the patient.
  - d) The patient has lost contact.
  - e) The investigator confirms that the AE is not related to the trial treatment.
  - f) The patient starts a new anti-cancer treatment.
  - g) The study is over.

Any AE should be recorded in detail on the eCRF and reported in the clinical research report.

If a large number of unexpected AEs related to the study drug occur during the research period, it is required to immediately report to the Institutional Review Board (IRB)/Independent Ethics Committee (IEC), the Chinese Food and Drug Administration (CFDA) and relevant supervision and management department of provinces, autonomous regions, and municipalities.

### **8.2.7 Handling and report of serious adverse events**

According to the Chinese GCP regulations, all SAEs that occur during clinical research, in addition to the treatment of AEs in Section 8.2.6, the following measures should also be taken:

1. The investigator must report any SAE (whether it is considered to be related to the study drug or not) within 24 hours and record it on the AE page of the CRF.
2. All SAEs should be followed up as far as possible until alleviation,

improvement to baseline level, death or loss of contact of the patient. SAEs that are considered as irrelevant to the study treatment by the research still require follow-up. After the follow-up period is over, with enough reasons to rule out relevance of SAE to the study drug, it should still be reported in the same way.

### **8.2.8 Pregnancy**

In order to ensure the safety of patients, pregnancy that occurs during the trial treatment must be reported to the investigator within 24 hours of notification. At the same time, the pregnancy must be visited to clarify the outcome, including spontaneous or induced abortion, details of childbirth, congenital malformations or comorbidities of the mother or newborn.

After the pregnancy occurs, the researcher must fill out the pregnancy report to record the details of the pregnancy and its visits. SAE during pregnancy should also be reported on the SAE report. The investigator should report to Innovent within 24 hours of notification of pregnancy and fill out the "Innovent Clinical Trial Pregnancy Report/Follow-up Form".

If a male patient participates and receives the study drug in the trial, his female partner becomes pregnant, the investigator should report to Innovent within 24 hours of notification of pregnancy, fill out the "Innovent Clinical Trial Pregnancy Report/Follow-up Form" and collect information of pregnancy outcome. Prior to this, the male subject and his female partner must sign an informed consent form agreeing to provide the pregnancy outcome information.

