- Physical examination and ECOG score: general physical examination was performed during screening period, study treatment termination visit and safety follow-up, and lymphoma specialist physical examination was performed during treatment.
- Treatment: should be administered on the first day of each cycle after all clinical and laboratory procedures / assessments are completed.
- Pregnancy test: fertile female subjects were required to conduct hCG pregnancy test during screening period (within 7 days before the first administration), study treatment termination visit and safety follow-up. When there are clinical indications, follow-up urine pregnancy test should be carried out. If urine pregnancy test is positive, serum pregnancy test should be carried out.
- Blood routine, biochemical routine, urine routine, blood coagulation, thyroid function was detected at - 2 to 0 days before each cycle.

13. Pulmonary function: during the screening period (within 28 days before the first administration) and the treatment period (12 weeks)  $\pm$  7 days) and safety follow-up.
14. During screening period, patients with hepatitis B positive need to be rechecked in treatment termination and safety follow-up.
15. HBV-DNA positive patients should be monitored every cycle of treatment and treated with nucleoside analogues
16. EBV-DNA: In the screening period, the plasma EBV-DNA was monitored. Before every course of treatment and the first day of the follow-up course were monitored. After all courses of treatment, the patients were monitored once a month according to the fixed time.

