### **3.5 Follow-up Period**

All patients, regardless of disease status, will be visited for end of treatment within 4 weeks after the end of the study, followed every 12 weeks for up to 3 years, or until withdrawal of consent, loss to follow-up, or death, whichever occurs first. When disease assessments are not planned for a follow-up visit, the visit can be done by phone.

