- c) Platelet count  $\geq 75 \times 10^9$  / L for subjects without marrow involvement of lymphoma; platelet count  $\geq 50 \times 10^9$  / L for subjects with marrow involvement;
  - d) Upper Limit Normal (ULN), or creatinine clearance ( $\geq 40$  mL/min) of serum creatinine ( $\leq 1.5$  times normal value upper limit) (estimated by the Cockcroft-Gault formula);
  - e) Serum total bilirubin  $\leq 1.5$  times ULN;
  - f) Aspartate Aminotransferase (AST), Alanine Aminotransferase (ALT)  $\leq 2.5$  times ULN;
  - g) Coagulation function: International Normalized Ratio (INR)  $\leq 1.5$  times ULN; Prothrombin Time (PT), Activated Partial Thromboplastin Time (APTT)  $\leq 1.5$  times ULN (unless the subject is receiving anticoagulant therapy and PT and APTT are using anticoagulant therapy at the screening time).
  - h) Thyroid-stimulating hormone (TSH) or free thyroxine (FT4) or free triiodothyronine (FT3) are all within the normal range ( $\pm 10\%$ ).
9. There was no evidence that subjects had difficulty breathing at rest, and the measured value of pulse oximetry at rest was more than 92%;
10. Subjects must pass a pulmonary function test (PFT) to confirm that forced expiratory volume (FEV1)/forced vital capacity (FVC) in the first second is more than 60%, unless it is a large mediastinal mass caused by lymphoma that cannot meet this standard; carbon monoxide diffusion (DLCO), FEV1 and FVC are all above 50% of the predicted value; all PFT results must be obtained within four weeks before the first administration;

11. Subjects who have received anti-tumor therapy should be screened only after the toxicity of the previous treatment has recovered to the grade 1 level or baseline level according to Common Terminology Criteria for Adverse Events (CTCAE) V5.0;
12. Women of Childbearing Potential (WOBCP) must undergo a serum pregnancy test within seven days before the first medication and the results are negative. WOBCP or men and their WOBCP partners should agree to take effective contraceptive measures from the signing of ICF until six months after the last dose of the research drug is used.

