### **8.2.2 Definition of serious adverse events**

Serious adverse events were the following AEs at any dose:

- a) Results in death.
- b) Life threatening.
- c) Note: The term "life-threatening" in the definition of "serious" means that the patient is at risk of death when the event occurs, and does not mean death if the event is more serious.
- d) Need to be hospitalized or extend the length of hospitalization.

**Note:** Generally speaking, hospitalization refers to patients staying in a hospital or emergency ward (generally at least overnight) and/or receiving treatment that is not suitable for conduction in doctor's office or outpatient department. Complications that occurred during hospitalization were AEs. If the complication prolongs the hospital time or meets any other serious criteria, the event is an SAE. When it is uncertain whether it should be "hospitalized" or required for "hospitalization", the AE

should also be regarded as an SAE.

Hospitalization due to selective treatment or pre-existing disease that has not worsened than baseline is not an AE.

- e) Results in disability/dysfunction.

**Note:** The term “disability” refers to severe influence of an individual’s ability to conduct normal life functions. This definition does not include events of relatively little clinical significance, such as simple headaches, nausea, vomiting, diarrhea, flu and accidental trauma (such as ankle sprains), which may affect daily function but dose not cause significant loss of function.

- f) Congenital malformations/birth defects.
- g) In other cases, medical or scientific judgment is required to determine whether to report. For example, it may not immediately threaten life or cause death or hospitalization, but it may threaten the patient or may require medical or surgical intervention to prevent the other important medical events listed in the above definition. These should also be considered SAEs, such as invasive or malignant tumors, allergic bronchospasm with intensive treatment in the emergency room or at home, blood disorders, convulsions that did not lead to hospitalization or drug dependence/abuse.

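### For female participants, section 8.2.8 ties pregnancy reporting and outcome follow-up to the treatment period, while inclusion criterion 12 requires contraception for six months after the last dose

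*Protocol*

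**What the plan says.** Inclusion criterion 12 (section 4.1, repeated in the synopsis) asks women of childbearing potential, and men with such partners, to use "effective contraceptive measures from the signing of ICF until six months after the last dose of the research drug". This is the only place where the protocol says how long after dosing it regards pregnancy as something to avoid.

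Section 8.2.8 opens with the rule for participants: "pregnancy that occurs during the trial treatment must be reported to the investigator within 24 hours of notification". It continues: "At the same time, the pregnancy must be visited to clarify the outcome". Later sentences ask for a pregnancy report form and a report to the company within 24 hours, and state no window of their own. A separate paragraph covers partners: "If a male patient participates and receives the study drug in the trial, his female partner becomes pregnant", the investigator reports to the company and collects the outcome. That paragraph has no end date.

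On testing, the flow-chart row marks screening and end of treatment only. Its note says that "fertile female subjects were required to conduct hCG pregnancy test during screening period", and adds the treatment termination visit and the safety follow-up, which is set at 30 ± 3 days after the last treatment. The note also calls for a urine test when clinically indicated, with no end date. Section 6.3 includes a serum pregnancy test in an end-of-treatment visit that may fall within 8 weeks.

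On serious events, section 8.2.2 lists "Congenital malformations/birth defects" among the criteria. The adverse-event note to the flow chart records serious events to 90 days after the last treatment or to new anti-tumour treatment, whichever is first, and only treatment-related ones after that.

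**The concern.** The contraception rule and the pregnancy-reporting rule address the same exposure risk but cover different periods. A woman who conceives two months after her last dose is inside the period for which the protocol requires contraception. She is outside the only sentence that obliges anyone to report her pregnancy and learn its outcome.

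Section 8.2.8 is also uneven within itself. On its wording, the partner of an exposed man is covered for longer than a woman who was exposed directly, and no reason is given.

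At stake is the completeness of the safety profile, which is a secondary objective. Exposed pregnancies are rare, and each is informative. If a site follows 8.2.8 to the letter and does not send the case, it is unlikely to be recovered later.

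**Working it through.** The protocol gives no figure of its own to reproduce on this point. The check compares windows, counted in days from the last dose.

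**Inputs**
- Contraception window W: six months, taken as 180 to 183 days (assumption). Source: section 4.1, criterion 12.
- Pregnancy reporting, female participants: during trial treatment, so 0 post-dose days on a literal reading. Source: section 8.2.8.
- Last scheduled test: day 30, at the latest day 33. Source: flow chart and its pregnancy-test note.
- Last scheduled test if the section 6.3 visit is used: up to 8 weeks = 56 days. That section counts from the end of the study; counting from the last dose is an assumption.
- Recording of all serious events: to day 90, or earlier if new anti-tumour treatment starts. Source: flow-chart adverse-event note.

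**Formula:** uncovered share = (W − last covered day) / W

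| Provision | Last covered day | Uncovered days | Uncovered share |
|---|---|---|---|
| Reporting duty, female participants | 0 | 180 to 183 | 100% |
| Scheduled test, safety follow-up | 30 to 33 | 180 − 33 = 147 to 183 − 30 = 153 | 147/180 = 81.7% to 153/183 = 83.6% |
| Scheduled test, 8-week visit | 56 | 180 − 56 = 124 to 183 − 56 = 127 | 68.9% to 69.4% |
| All serious events recorded | 90 | 180 − 90 = 90 to 183 − 90 = 93 | 50.0% to 50.8% |

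**Whether other provisions close the reporting gap for female participants**
- *Adverse-event collection.* Section 8.2.1 ends it 30 days after medication. Section 8.1 ends safety monitoring 4 weeks after treatment, or at a new anti-tumour treatment if that is earlier. Neither reaches six months.
- *Serious-event rules.* An uncomplicated pregnancy meets no criterion in section 8.2.2, so these rules do not pick it up. A birth defect does meet one. If it follows a post-treatment conception it would appear well after day 90, when the flow-chart note keeps only related events. Section 8.2.7, item 2, is wider: it still asks for reports after follow-up has ended.
- *Follow-up contacts.* Under section 3.5 patients are "followed every 12 weeks for up to 3 years". The survival column of the flow chart contains only new anti-cancer therapy and survival status, and section 6.5 collects the same two items after progression. Nothing prompts a question about pregnancy.

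**Which contacts fall within about 26 weeks.** The protocol's schedules differ:
- flow chart and section 3.5, every 12 weeks: weeks 12 and 24;
- sections 3.1 and 6.4, first at week 8 and then every 12 weeks: weeks 8 and 20;
- flow-chart survival note and section 6.5, every 8 weeks after progression: weeks 8, 16 and 24;
- section 3.6 ends the study 8 weeks after the last enrolled patient's last medication, so late contacts may not happen for the last patients.

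**The case against.** The strongest reply is that little is lost. Partner pregnancies are fully covered. A serious outcome that reaches the investigator has a route through sections 8.2.2 and 8.2.7 and the flow-chart note. Urine tests on clinical indication have no end date. The sentence asking for a report to the company within 24 hours does not itself exclude a pregnancy notified after treatment. Patients are required to use contraception throughout, and section 10.1 plans only 37 to 46 patients before allowing for loss.

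Much of this stands, and it rules out several stronger readings that a reader might infer:
- *That all exposed pregnancies go unreported.* The partner paragraph contradicts this. Applying a six-month limit to partners as well would shorten a duty that now has no end.
- *That a birth defect would never be recorded.* The serious-event rules give it a route, although that route depends on someone bringing it to the investigator and, under the flow-chart note, on its being judged related.
- *That about 83% of exposed pregnancies would be missed.* The figure is a share of calendar days without a scheduled test after the 30-day visit. It says nothing about the number of events, and it falls to about 69% under section 6.3.
- *That contacts at weeks 12 and 24 are already fixed.* The schedules conflict, so this is not established.

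The reply does not remove the limit in the first sentence of 8.2.8. The later company-report sentence reads most naturally as referring to the same pregnancy, and a test done on indication is not a duty to report its result.

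**Conclusion.** The mismatch is real but narrow. For female participants, the stated duty to report a pregnancy and follow its outcome covers none of the six post-dose months during which criterion 12 requires contraception. What is lost is mainly the routine report and follow-up of an uncomplicated pregnancy that begins after treatment. No scheduled test falls in roughly 69% to 84% of that period, depending on which visit timing applies.

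This rests on a literal reading of section 8.2.8, on six months as 180 to 183 days, and on counting the section 6.3 visit from the last dose. The expected number of events is small; the protocol gives no basis for a count. The primary endpoint, the sample size and the decision rule are unaffected. It is worth correcting because the change is very cheap and a missed case is hard to recover.

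**What to change.** - In the first sentence of section 8.2.8, replace the limit to the treatment period, for female participants, with a window from first dose to the end of the post-dose contraception period in criterion 12. A cross-reference to criterion 12 would keep the two aligned. The outcome follow-up already described then applies to the same window.
- Leave the paragraph on partners of male patients as it is.
- Add one pregnancy question, where applicable, to whichever existing follow-up contacts fall within six months of the last dose. Word it that way and not by week number, because the contact schedules in sections 3.1, 3.5, 3.6, 6.4 and 6.5 and the flow chart still have to be reconciled.

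The cost is one reworded sentence and one question on the follow-up form. No extra test is needed, and no extra visit wherever a contact already falls in the window. For the last patients enrolled, that depends on how section 3.6 is reconciled with the follow-up schedule. Neither treatment nor the contraception requirement changes.
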